#### Study integrity

This study is listed on the Australian New Zealand Clinical Trials Registry ACTRN12613000270718, and has undergone rigorous multidisciplinary peer and consumer review. It is endorsed by the Australian New Zealand Children’s Haematology Oncology Group (ANZCHOG).

Ethical approval has been obtained from Sydney Children’s Hospital, Children’s Hospital at Westmead, Royal Children’s Hospital Melbourne, Monash Children’s Hospital Melbourne, Queensland Children’s Cancer Centre, Women’s and Children’s Hospital Adelaide, and the Royal Adelaide Hospital. This study complies with the CONSORT guidelines [42] by using the following: a) standardised assessment measures; b) blind assessments; c) standardised assessor training and inter-rater reliability checks; d) manualised, replicable procedures for all conditions; e) random allocation; and f) treatment fidelity checks.

#### Treatment fidelity

Both treatment groups will be facilitated by the same person to prevent confounds (for example, attributes such as age, sex and communication style), each of which could impact group retention/efficacy. Any variation or systematic biases between groups will be detected and corrected by the independent assessors during treatment fidelity checks of a random 15% of all video-recorded sessions (the validated ‘Method of Assessing Treatment Delivery’ advises a minimum of 11%) [51]. All pre- and post-treatment outcome measures will be administered by the research officer, who will be blind to group allocation. In compliance with the CONSORT guidelines, the research officer will report on which condition they believe each participant was in at the end of the study.

To ascertain why this intervention may not be tolerated by all parents, exit interviews will be collected for all who leave the study prematurely, as well as for 15% of those who complete the intervention to collect in-depth data on participants’ likes and dislikes and to solicit ideas for improvement.

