**Table 1 Tab1:** **Assessment schedule for the cascade study**

**Measure**	**Intake**	**Q1** ^**a**^	**During intervention** ^**b**^	**Q2** ^**c**^	**Q3** ^**d**^	**Q4** ^**e**^	**Q5** ^**f**^
Psychosocial Adjustment to Illness Scale-Interview form (PAIS)	**X**	**-**	**-**	**-**	**-**	**-**	**-**
Demographic data	**-**	**X**	**-**	**-**	**-**	**-**	**-**
Treatment Intensity Scale	**-**	**X**	**-**	**-**	**-**	**-**	**-**
Medical and general functioning^g^	**-**	**X**	**-**	**X**	**X**	**X**	**X**
Paediatric Quality of Life Inventory (PedsQL) Generic Core Scale^h^	**-**	**X**	**-**	**X**	**X**	**X**	**X**
Paediatric Quality of Life Inventory (Family Impact Module)	**-**	**X**	**-**	**X**	**X**	**X**	**X**
EQ-5D-5 L	**-**	**X**	**-**	**X**	**X**	**X**	**X**
Parenting Self Agency Measure (Revised)	**-**	**X**	**-**	**X**	**X**	**X**	**X**
CBT skills use	**-**	**X**	**-**	**X**	**X**	**X**	**X**
PROMIS parent mental health and functioning short-form items^i^	**-**	**X**	**-**	**X**	**X**	**X**	**X**
California Psychotherapy Alliance Scale - Group (CALPAS-G)	**-**	**-**	**-**	**X**	**-**	**-**	**X**
Intervention satisfaction items	**-**	**-**	**-**	**X**	**-**	**-**	**X**
Emotion Thermometers Tool	**X**	**-**	**X**	**-**	**-**	**-**	**-**
Homework Compliance Scale	**-**	**-**	**X**	**-**	**-**	**-**	**-**
Working Alliance Inventory - Short	**-**	**-**	**X**	**-**	**-**	**-**	**-**

^**a**^Q1 = Baseline; ^**b**^During intervention = weekly prior to intervention sessions 2 to 4; ^**c**^Q2 = post-intervention.

^**d**^Q3 = Week 5 follow-up, ^e^Q4 = 6 month follow-up; ^f^Q5 = after waitlist participants have completed the intervention.

^g^Including other psychological support received; ^h^Parent proxy and child self-report; ^i^Items assess parent depression and anxiety symptoms.

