### Procedures

Following recruitment, participants will complete a telephone intake interview with a Cascade research officer to further screen for participant eligibility, orient participants to the study procedures, ascertain any technical needs, and complete the PAIS [40].

Participants will then be randomly allocated to a study arm. During Weeks 1 to 4 of each 12-week block, those allocated to Cascade and the PSG will participate in their allocated intervention. Waitlist controls will be assessed at the same time points as the intervention groups, and will be randomly allocated to either Cascade or PSG during weeks 26 to 30. The waitlist group will also complete a final questionnaire (Q5) after participating in the intervention. Parents will be sent links via email to complete the questionnaires (see *Data management and analysis*) and will be encouraged to supervise their child/ren while they complete the questionnaires, if desired.

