### Data management and analysis

All measures (excluding the PAIS telephone interview) will be administered online through Key Survey (WorldAPP, Braintree, MA, USA) at all time points, unless paper versions are requested by participants. Key Survey enables participants’ data to be securely downloaded to files amenable to statistical analysis using the Statistical Package for the Social Sciences, version 18.0 (SPSS, Inc., Chicago, IL, USA).

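### The article presents outcome assessment as blind, but every efficacy questionnaire after randomisation is completed by families who know whether they are in a programme or waiting

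*Protocol article*

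**What the plan says.** The protocol article makes the blinding claim in two places. Study integrity lists "b) blind assessments; c) standardised assessor training and inter-rater reliability checks" among the ways in which the trial meets the CONSORT guidelines. Treatment fidelity states: "All pre- and post-treatment outcome measures will be administered by the research officer, who will be blind to group allocation". The same section has the officer record, at the end of the study, which condition they think each participant was in.

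Other sections describe how the data are collected. Procedures says: "Parents will be sent links via email to complete the questionnaires". Data management and analysis says: "All measures (excluding the PAIS telephone interview) will be administered online through Key Survey", with paper versions for participants who ask for them. Table 1 marks the PAIS at intake and at no later assessment. Procedures places the intake interview, including the PAIS, first and continues: "Participants will then be randomly allocated to a study arm".

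The section on parent functioning names the PedsQL Family Impact Module as the primary outcome variable. The section on child functioning describes a parent proxy form and a child self-report form.

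**The concern.** Blind assessment protects a trial when the person who judges the outcome does not know the allocation. Here the parent judges the primary outcome, and the parent knows whether sessions were attended or a six-month wait was imposed. The article describes no blinding of participants.

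At stake is how the efficacy results will be read. Hypothesis 1 compares both Cascade and peer support with the waitlist on change from T1 to T2, the interval of the primary analysis. Parents who received a programme may report improvement because they expect it, and parents who are waiting may report less because they are disappointed. A reader told that assessments were blind would take this bias as controlled. The Discussion's account of methodological vulnerabilities does not mention unblinded self-report, so nothing there corrects the impression.

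**Working it through.** **Who supplies each outcome, and when**

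| Item | Source in the article | Supplied by | Timing |
|---|---|---|---|
| PAIS | Table 1; Procedures | Telephone interview by the officer | Intake only, before allocation |
| PedsQL Family Impact Module (primary) | Table 1; parent functioning | Parent | Q1 to Q5 |
| EQ-5D-5L, parenting self-agency, PROMIS depression and anxiety items, CBT skills use | Table 1; parent functioning; intervention engagement | Parent | Q1 to Q5 |
| PedsQL Generic Core | Table 1; child functioning | Parent proxy and child | Q1 to Q5 |
| Feasibility measures (e.g. attrition, response rate) | Feasibility | Recorded by the study | Throughout |

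1. The PAIS is the only measure exempted from online completion. It precedes allocation, so blinding cannot affect it.
2. Every efficacy measure from Q2 onward is completed by the family through emailed links, or on paper if requested. The article describes no officer rating of any of them.
3. Treatment fidelity says that the officer administers all outcome measures, while Procedures and Data management and analysis describe emailed links to an online survey. These can be reconciled only if administering means sending and chasing links. In that sense the officer's blinding covers contact with families and not the answers.
4. The parent who answers has attended sessions or is waiting. Knowledge of allocation is therefore built into both contrasts with the waitlist.
5. Cascade versus peer support differs. The design section says that the peer-support arm holds contact constant and controls for the expectation of treatment. The article does not say whether parents know which programme is under test.

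**The plan's own figure**

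Inputs from Participants: d = 0.65 on T1 to T2 change, two-sided alpha 0.05, power 80%, about 40 per arm.

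- Normal approximation: n per arm = 2 × (1.960 + 0.842)² / 0.65² = 15.70 / 0.4225 = 37.2, so 38.
- Exact noncentral t: 39 per arm are needed. Power at 40 per arm is 81.9%.

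The stated 40 per arm is reproduced. The blinding point does not depend on it.

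**Illustration of size (assumed shift, not in the documents)**

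Let b be a difference in reporting between treated and waiting parents, in the SD units of the sample-size statement, with no true effect. With 40 per arm the noncentrality is b × √(40/2) = 4.472b, on 78 degrees of freedom.

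| b (SD) | b / 0.65 | Noncentrality | Two-sided rejection rate at nominal 5% |
|---|---|---|---|
| 0 | 0% | 0 | 5.0% |
| 0.1 | 15% | 0.447 | 7.3% |
| 0.2 | 31% | 0.894 | 14.3% |
| 0.3 | 46% | 1.342 | 26.3% |
| 0.4 | 62% | 1.789 | 42.4% |

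These rates are for one contrast at unadjusted 5%. They leave out the planned Holm-Bonferroni adjustment, which would lower them. Blinding the officer would not change b where it arises in the respondent.

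**The case against.** The best defence is that the article claims blinding for the research officer only. It never says that parents are blind or that officer blinding removes self-report bias. Quality of life has to be self-reported, parents cannot be blinded to waiting, and this is usual in psychological trials. Expectation is also addressed by design: the peer-support arm exists partly for that purpose, and the Discussion gives the waitlist a different role, to control for distress that fades naturally and for changes in services.

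Much of this stands. The design is not at fault, and the Cascade versus peer-support contrast deserves credit. What does not stand is the unqualified listing of blind assessments as a safeguard when the blinded person rates no efficacy outcome after allocation.

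A reader might infer more than the documents support:

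- **That no trial outcome is protected, or that officer blinding is worthless.** Feasibility is a stated aim and its measures are recorded by the study. A blind officer may also prompt and follow up families more evenly.
- **That the inter-rater item is empty.** The article does not say which ratings "standardised assessor training and inter-rater reliability checks" covers. It could mean the PAIS interview or the ratings of session videos. Fidelity checks are listed separately, but that does not settle the matter.
- **That the officer's end-of-study guess tests the wrong person.** It tests the officer's blinding, which is what Treatment fidelity claims.
- **That alliance and satisfaction items at Q2 unblind the officer.** Nothing says that the officer reads the responses, and the point is secondary if the officer does not rate the outcomes.

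**Conclusion.** The point holds for the efficacy questionnaires. The article claims blind assessment, and its own account of data collection shows that the primary outcome and the other efficacy questionnaires after randomisation are unblinded self- or proxy-report. The consequence is greatest for Cascade versus waitlist and peer support versus waitlist, and smaller for Cascade versus peer support.

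The size of any bias cannot be derived from the documents. An assumed shift of 0.1 to 0.3 SD gives 15% to 46% of the design effect and a false-positive rate of about 7% to 26% per unadjusted contrast. This shows what could be at stake and does not estimate bias in this trial. The conclusion rests on two readings: that families know whether they are attending sessions or waiting, which follows from the design, and that the officer does not score the online responses, since no such scoring is described. No change to the sample size or the primary analysis follows.

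**What to change.** - Reconcile the statement in Treatment fidelity that the officer administers all outcome measures with the emailed online questionnaires in Procedures and in Data management and analysis.
- In Study integrity and Treatment fidelity, limit the blinding claim to the research officer and name the tasks that it covers.
- State that the primary outcome and the other questionnaire outcomes are unblinded parent self-report, parent proxy-report or child self-report.
- Label the Cascade-waitlist and peer-support-waitlist contrasts as open-label and exposed to expectation effects. Note that the matched active control gives the Cascade versus peer-support contrast better protection.
- Name unblinded self-report among the limitations.
- Say which ratings the inter-rater checks cover; the item need not be deleted.
- Keep the officer's end-of-study guess as a check on the officer's blinding.

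An expected-benefit question at T1 would not serve as a check on blinding. T1 is completed around the intake call, before allocation, so arms could differ on it only by chance.

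The cost is wording, which can be changed while recruitment continues. The price is a less favourable statement of the trial's rigour.

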#### Safety monitoring

This trial includes safety monitoring and management procedures at multiple project stages (see Figure 2). The intake interview carefully screens for acutely suicidal/severely depressed participants. Participants will also be regularly screened for mood deterioration during intervention participation when they complete the weekly Emotion Thermometers Tool [39] (see *Assessments*). Any deterioration in mood of more than three points on the tool will trigger protocols involving the facilitator contacting the participant to discuss their emotional state and a meeting between the researchers to develop a management plan (which may include contacting their nominated health professional, with the participant’s consent).

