## Methods/Design

The Cascade study is a multi-site, randomised controlled trial (RCT) to assess the feasibility and efficacy of a new, online, CBT-based intervention for the parents or legal guardians (hereafter referred to as ‘parents’) of young cancer survivors (see Additional file 1 for a list of participating centres and ethical bodies). Parents of children under 16 years of age who have completed cancer treatment with curative intent and achieved remission in the past 12 months will be recruited and randomised to one of three arms: i) Cascade, ii) a peer-support group (PSG) control, or iii) a 6-month waitlist control. Informed consent will be obtained from all participants. The 1- to 12-month timeframe was chosen to maximise the benefit to participants, by delivering the coping skills intervention early in their child’s survivorship period. The intervention, named ‘CASCAdE’ (*C*ope, *A*dapt, *S*urvive: Life after *CA*nc*E*r), is delivered live, in real-time, to groups of 3 to 5 parents by a psychologist (hereafter referred to as ‘facilitator’) in four, weekly online sessions. Participants also receive an online introductory session with the facilitator before the group commences and a ‘booster’ session one month after the end of the group to facilitate consolidation of skills.

Cascade will be compared with the active PSG control in order to assess the relative benefits of peer-based support and contact with any additional psychological benefits gained from learning structured, skills-based coping strategies. ‘Peer-support’ type models of support are ubiquitous in community settings, yet few PSGs have been rigorously evaluated [36]. Consequently, little evidence exists to support the appropriateness of PSGs alone in addressing distress in parents of children with cancer. The PSG arm holds constant the amount of treatment contact, human interaction variables (such as facilitator warmth and interaction between participants), as well as controlling for participants’ expectations of receiving some form of treatment [37].

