#### Exclusion criteria

Parents will be excluded if, during the initial intake interview, they i) have insufficient English language skills to complete the interview; ii) demonstrate very high levels of distress, anxiety, and/or depression on the Emotion Thermometers Tool (that is, scores ≥ 7) [39] and endorse serious suicidal intent; iii) endorse symptoms of psychosis or substance abuse; or iv) have a child who is currently on active treatment, has relapsed, or is in palliative care. Any participant who is excluded will be provided with appropriate referral options, if desired.

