Participants randomised to Cascade will participate in four, live, weekly, 90-minute sessions facilitated by a psychologist. Each group will comprise a psychologist and three to five participants with mixed cancer experiences (such as the age of their child and their child’s type of cancer). Participants also receive a purposely developed workbook, outlining the content of each session, providing additional examples and suggesting ‘homework’ activities to facilitate skill development. Additional files 2, 3 and 4 show details of the workbook content and graphic design.

Sessions will be delivered through WebEx (Cisco WebEx, USA). WebEx requires a computer with standard browser, a high-speed internet connection, and a webcam. WebEx is a secure, password-protected video-conferencing program that allows up to six participants to be seen on the screen simultaneously, similar to group Skype™. Participants will receive a reminder text message on their cellular phone 24 hours before their session, which will also serve as their reminder to complete the Emotion Thermometers Tool [39] and homework compliance scale (see *Assessments*).

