#### Intervention engagement and impact

To assess participants’ mood in a more dynamic manner across the intervention, parents will complete the Emotion Thermometers Tool [39] each week, 24-hours prior to participating in their weekly session (Cascade or PSG). At the same time, parents will complete the 6-point Homework Compliance Scale [64] to assess compliance with the home practice exercises. CBT skills used will also be assessed using 10 purposely developed and pilot-tested items; for example, assessing participants’ ability to ‘recognise unhelpful thoughts and how they are making me feel’ (response options range from ‘not at all’ to ‘a lot’). The Working Alliance Inventory - Short (WAI- S) [65] and The California Psychotherapy Alliance Scale - Group (CALPAS-G) [66] will be used to assess participants’ perceptions of the therapeutic working alliance, during and after the intervention.

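### Minor and conditional: if each Emotion Thermometer runs 0–10 and is scored separately, the mood trigger cannot fire on one that enters at 7 or above unless it first improves

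*Protocol article*

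**What the plan says.** The Safety monitoring section of the protocol article describes regular screening for falling mood while parents take part in the sessions. Its one score-based rule is a change rule: "Any deterioration in mood of more than three points on the tool will trigger protocols involving the facilitator contacting the participant". The same response includes "a meeting between the researchers to develop a management plan".

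The second exclusion criterion concerns parents who at intake show "very high levels of distress, anxiety, and/or depression on the Emotion Thermometers Tool", with the cut-off and a further condition given as "that is, scores ≥ 7) [39] and endorse serious suicidal intent". The two conditions are joined, so both must hold for exclusion under that item.

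The tool is completed at intake and again during the sessions. Table 1 places the later readings "weekly prior to intervention sessions 2 to 4"; the section on intervention engagement says "each week, 24-hours prior to participating in their weekly session". There are therefore three or four weekly readings after intake.

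The text does not give the range of the tool, the reading from which deterioration is counted, or whether the three points refer to one thermometer or to a total. Safety monitoring also refers to Figure 2, whose content was not available for this review.

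**The concern.** A rule based only on change needs room on the scale for the change to happen. Eligibility admits some parents whose score already lies in the band the protocol calls very high. If that band sits within three points of the top of the scale, the rule has no room to operate on the thermometer concerned, and a parent who worsens from a high start gets no score-based contact. A parent who moves the required distance from a low start does get it, even when the end score stays below the very-high band.

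What is at stake is detection of worsening during the sessions in parents who start out most distressed. The sample size, power and primary analysis are not affected.

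**Working it through.** **Inputs from the article**
- Trigger: worsening of more than 3 points, a strict inequality (Safety monitoring).
- Very-high band: 7 or above (Exclusion criteria).
- Exclusion under that item: 7 or above and serious suicidal intent (Exclusion criteria). A parent at 7 or above without such intent is therefore not excluded by it.

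**Assumptions, not in the article**
- Each thermometer runs from 0 to a maximum M = 10, in whole points.
- Thermometers are scored separately. The exclusion criterion applies a single cut-off of 7 to distress, anxiety and/or depression, which fits separate scoring but does not settle how the trigger is scored.

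**Step 1: room to worsen.** From entry score e, the largest possible worsening is M − e. The rule can fire only if M − e > 3.

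| Entry e | Room 10 − e | Can fire? |
|---|---|---|
| 6 | 4 | yes |
| 7 | 3 | no |
| 8 | 2 | no |
| 9 | 1 | no |
| 10 | 0 | no |

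So 2 to 6 (a rise of 4) fires, and 7 to 10 (a rise of 3) does not.

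**Step 2: does the reference reading matter?** Without prior improvement, the result is the same whether change is counted from intake, from the previous week or from the best earlier reading. After improvement it can differ: on the path 7, 5, 9 the change is +4 against the previous week or the best reading (fires) but +2 against intake (does not fire).

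**Step 3: other maxima.** Entry is blocked when e ≥ M − 3.

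| Maximum M | Blocked from |
|---|---|
| 8 | 5 |
| 9 | 6 |
| 10 | 7 |
| 11 | 8 |
| 12 | 9 |

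Entry at 7 can fire only if the maximum is 11 or more.

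**Step 4: a summed score.** On a sum of the three named thermometers (0–30), a parent at 7, 7, 7 has 30 − 21 = 9 points of room and could trigger. Only a parent at a total of 27 or more would be blocked (30 − 27 = 3).

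**Step 5: possible worsenings with M = 10.** There are 55 whole-point pairs in which the later score exceeds the entry score. A rise of at least 4 occurs in 7 + 6 + 5 + 4 + 3 + 2 + 1 = 28 of them.

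| Type of worsening | Pairs | Rule fires |
|---|---|---|
| Starts at 7 or above | 6 | 0 |
| Crosses from below 7 to 7 or above | 28 | 22 |
| Ends below 7 | 21 | 6 |
| Total | 55 | 28 |

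These count possibilities. They say nothing about how often each would occur.

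**The case against.** The strongest objection is that the missing piece may lie in material not available here. Safety monitoring refers to Figure 2, and the trigger starts protocols that may be set out elsewhere. This stands as a limit: nobody can say from the text alone that the trial lacks a trigger based on level. It does not remove the point, because the change rule is stated in full in the text and on the assumed scale does not work for high entrants.

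Second, the block depends on two unstated facts. A maximum of 11 or more frees entry at 7, and a total score would largely remove the problem. The rule speaks of points on the tool, which could mean a total. This also stands and is why the point is conditional.

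Third, other safeguards remain. Intake screens for acutely suicidal and severely depressed parents, and both intervention arms meet the same psychologist live each week. The Methods/Design section adds, in describing Cascade, "Participants also receive an online introductory session with the facilitator before the group commences". Another thermometer that entered at 6 or below may still trigger for the same parent. These safeguards reduce the consequence, although the only exclusion rule stated for high scores still needs both conditions.

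A reader might infer more than the documents support:
- **That very distressed parents go unmonitored.** They do not; only the score rule, on the thermometer concerned, is blocked.
- **That a score which stays high should trigger.** The rule is about deterioration, and a steady score is not deterioration.
- **That crossing from below 7 to 7 or above should trigger.** The rule already fires on 22 of those 28 pairs. Flagging the other 6 would replace the protocol's threshold with a different clinical preference and has nothing to do with the ceiling.

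**Conclusion.** The point holds as a minor, conditional one. On the text's wording, and if each thermometer runs 0–10 and is scored separately, the trigger cannot fire on a thermometer that enters at 7 to 10 unless that thermometer improves first. It then fires on none of the 6 possible worsenings inside the band the protocol calls very high.

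The number of parents affected cannot be given, because the article does not report how many enrol at 7 or above. Figure 2 may already close the gap. The point is worth raising because it concerns participant safety and the remedy is cheap; it is not evidence that the safety monitoring as a whole fails.

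**What to change.** Check Figure 2 first. If it already has a rule for parents who enter at 7 or above, one sentence in Safety monitoring pointing to it is enough.

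Otherwise add two statements to that section:
1. For a thermometer that entered at 7 or above, any rise above its highest reading so far triggers the same facilitator contact.
2. The three points are counted per thermometer.

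No new assessment is needed, since the scores are already collected; the text message before each session is one "which will also serve as their reminder to complete the Emotion Thermometers Tool". Under the assumptions above, the flagged set grows from 28 to 28 + 6 = 34 of 55 possible worsenings, and all 6 additions lie inside the very-high band.

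The cost is a few extra facilitator contacts and, because the triggered response includes them, extra management-plan meetings. Tying the rule to new highs limits this. With readings before sessions 2 to 4, a thermometer steady at 8 gives 0 triggers, and the path 7, 10, 10, 10 gives 1. A rule on any weekly score of 7 or more would give 3 in each case. A one-point rise such as 7 to 8 would prompt contact, which is the price of covering a band with so little room.
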